## Abstract

**Introduction:**

Sub-Saharan Africa is experiencing an increasing burden of diabetes, but there are
little reliable data, particularly at the community level, on the true prevalence or why
this condition affects young and relatively lean individuals. Moreover, the detection of
diabetes in Africa remains poor, not only due to a lack of resources but because the
performance of available diagnostic tests is unclear.

**Methods:**

This research aims to (1) determine the prevalence and risk factors of diabetes in a
rural Ugandan population, (2) use clinical and biochemical markers to define different
diabetes phenotypes and (3) study the progression of diabetes in this population. We
will also assess the utility of the widely used tests (glycated haemoglobin (HbA1c),
oral glucose tolerance test (OGTT) and fasting glucose) in diagnosing diabetes.

**Design:**

This is a population-based study nested within the longstanding general population
cohort in southwestern Uganda. We will undertake a population survey to identify
individuals with diabetes based on fasting glucose, HbA1c, OGTT results or history of
pre-existing diabetes.

**Participants:**

The study intends to enrol up to 11 700 individuals aged 18 years and above,
residing within the study area and not pregnant or within 6 months post-delivery
date. All participants will have detailed biophysical and biochemical/metabolic
measurements. Individuals identified to have diabetes and a random selection of controls
will have repeat tests to test reproducibility before referral and enrolment into a
diabetic clinic. Participants will then be followed up for 1 year to assess the
course of the disease, including response to therapy and diabetes-related
complications.

**Conclusions:**

These data will improve our understanding of the burden of diabetes in Uganda, the risk
factors that drive it and underlying pathophysiological mechanisms, as well as better
ways to detect this condition. This will inform new approaches to improve the prevention
and management of diabetes.

**Ethics and dissemination:**

This study protocol was approved by the Uganda Virus Research Institute Research Ethics
Committee (REC) (number: G.C./127/21/09/858), the London School of Hygiene and Tropical
Medicine REC (number: 26638) and the Uganda National Council for Science and Technology
(protocol number: HS1791ES). Written informed consent will be obtained from all
participants before being enrolled on to the study and conducting study-related
procedures. Research findings will be disseminated in policy briefs, seminars, local and
international conferences and publications in peer-reviewed open-access journals. As
part of the dissemination plans, findings will also be disseminated to patient care
groups and to clinicians.

**Trial registration number:**

NCT05487079.

STRENGTHS AND LIMITATIONS OF THIS STUDYThe large sample size gives sufficient power to answer the primary and secondary
research questions.This project will provide a characterised cohort of individuals with diabetes who will
be followed up for future research.Biospecimens will be stored for future research purposes.This study is nested in a longstanding and well-characterised general population cohort
with routine follow-ups.Participants could be lost to follow-up which may impact on the study power and may
introduce bias.

## Introduction

Diabetes is a global problem disproportionately affecting low-income and middle-income
countries (LMICs). According to the 2021 International Diabetes Federation estimates,
80% of the approximately 537 million adults (20–79 years) living with
diabetes reside in LMICs.^1^ In sub-Saharan Africa
(SSA), an estimated 24 million people are living with diabetes, which is projected to
reach 55 million within 20 years.^1^ Moreover,
the region is said to harbour the highest proportion of undiagnosed patients with
diabetes.^1^ This poses a major threat to sustained
development in the region if resources have to be found to treat the complications of this
condition.

An effective response will require a clear understanding of the burden, important local
determinants of risk, and pathophysiological and clinical manifestations of diabetes.
However, there are limited Africa data, with most coming from relatively small studies using
unstandardised methodologies. This may explain the significant variation in diabetes
prevalence observed between countries.^2^ Moreover,
there are concerns that some of the widely used tests to diagnose and monitor diabetes may
be unreliable in Africa. Although still a relatively unexplored area, the clinical utility
of glycated haemoglobin (HbA1c) in SSA has been questioned due to the high prevalence of
haemoglobinopathies such as sickle cell trait and other medical conditions that might affect
test reliability, including anaemia, malaria and HIV infections.^3–6^ Similarly, there are concerns about the utility of
oral glucose tolerance test (OGTT), the current gold-standard test for diagnosing
diabetes.^7^ It is not only complex and expensive but
may have other important limitations, such as the need to have adequate caloric intake in
the days preceding the test. Our preliminary study showed that a missed or small meal the
night before a test could lead to falsely elevated glucose.^8^ This might explain why some Africa studies have found a high prevalence of
diabetes or glucose intolerance where OGTT has been used. Therefore, OGTTs cannot be fully
relied on to screen for diabetes in settings where food insecurity or missed evening meals
are common.

There is also increasing evidence that diabetes may manifest differently in Africa compared
with its presentation in high-income countries. For example, while traditionally, type 2
diabetes is considered a disease of old age associated with obesity and insulin resistance,
this condition appears to occur in relatively young and lean individuals in Africa and other
LMICs. This evidence initially came from Southeast Asia, where people were observed to
develop type 2 diabetes at lower levels of obesity than white Caucasians; this has led to
Asia-specific lower body mass index (BMI) thresholds for defining obesity.^9^ The explanation has been that Southeast Asians have a
propensity towards central obesity (and therefore insulin resistance) at relatively low body
weight. Our group recently showed that 50% and nearly 40% of newly diagnosed
type 2 diabetes (negative for pancreatic autoantibodies) in Uganda are younger than 50 years
and have a BMI of ≤25 kg/m^2^, respectively.^10^ In contrast to observations in Southeast Asia, the
‘thin’ patients showed no evidence of excess ectopic or visceral fat (using
anthropometric and electric bioimpedance measurements) or insulin resistance. Instead, they
had features consistent with insulin deficiency (lower fasting insulin, C peptide
insulinogenic index and Homeostatic Model Assessment for Insulin Resistance (HOMA-IR)).^11^

These observations raise important research questions and have huge potential clinical
implications: what are the mechanisms that drive diabetes in Africa; what are the right
approaches to its prevention and management? For example, are the lifestyle
interventions targeting weight loss or metformin use (as an insulin sensitiser), two
traditionally recommended first-line management options for type 2 diabetes, effective in
Africa?

This necessitates rigorous studies to unravel the complex manifestations of diabetes in
Africa and identify the right approaches to prevention and management. Therefore, in the
Diabetes in low-resource Populations Study, we aim to: (1) determine the prevalence of
diabetes in Uganda, (2) identify and characterise the different diabetes phenotypes, and (3)
develop a cohort in which we can examine and understand the course or progression of this
disorder and its different diabetes phenotypes. All patients except those with a known
diagnosis of diabetes (on oral or insulin treatment for diabetes) will undergo OGTT. With
this approach, we will be able to compare the diagnostic accuracy of fasting glucose and
HbA1c with OGTT.

## Research design and methods

### Study design

This will be a population-based study nested within the general population cohort
(GPC)—a longstanding population cohort study in southwestern Uganda.^12^

### Study setting

The study will be conducted in Uganda. Uganda is undergoing urbanisation, but more than
70% of the population still lives in rural areas. The study shall recruit from two
sites (rural and periurban areas) across the greater Masaka region in southwest Uganda to
explore the differences in lifestyle and how these influence the prevalence of diabetes
and its outcomes. The GPC in Kyamulibwa subcounty, Kalungu district in southwest Uganda,
will provide the rural population and the town of Lukaya, the periurban population. Both
rural and periurban sites are established research areas.

### Sample population

The GPC is a rural population-based open cohort study of people living within the 25
villages of the Kyamulibwa subcounty. The population in Kyamulibwa is assessed routinely
during annual surveys as part of the census and 2-year medical surveys. The entire adult
population of the GPC will be invited to participate in this study. Data from the most
recent census in the GPC study villages show that there are 8864 adults out of the total
population of 20 751. A recent enumeration for a COVID-19 survey conducted in
Lukaya established that there are approximately 10 000 adults in all the five
villages. All these will be invited to take part in our study. The combined adult
population within the GPC and Lukaya will give us enough power to rigorously examine our
primary objectives, allow explorations of the outcomes and key risk factors, and establish
long-term cohorts.

### Study objectives

#### Primary study objective

To determine the prevalence of diabetes and pre-diabetes in a population-based
cohort.

#### Secondary study objectives

To establish a cohort of well-characterised patients with diabetes to understand
disease progression and the course of the different phenotypes, including response
to treatment.To identify and recruit a cohort of individuals with pre-diabetes and volunteers
without diabetes for longitudinal follow-up.To assess the burden and rates of progression of vascular complications associated
with the different phenotypes of diabetes.

#### Primary study outcome

Prevalence of diabetes and pre-diabetes.

#### Secondary study outcomes

Number of distinct phenotypes of type 2 diabetes within this population.Baseline prevalence of vascular complications among individuals with diabetes.Rate of progression of vascular disease within this population.

### Sampling strategies

Recruitment will be restricted to individuals who reside within defined study areas.
Research team members (mobilisers) will visit each household in the study areas. All
adults aged 18 years and above will be invited to take part in the study (table 1). We will recruit every adult who is able and
willing to consent and is a resident at a household (ie, not a temporary member with
intent to leave) in the study areas. The participant’s flow in the study is shown
in figure 1.

**Table 1 T1:** Eligibility criteria for the participants enrolled into the DOP Study

Inclusion criteria	Individuals aged 18 years and above
	Individuals residing within the study area for the past 6 months
	Individuals willing to provide informed consent
Exclusion criteria	Pregnant women and women within 6 months post-delivery
	Participants unwilling to give informed consent
	Living outside the geographical sampling frame for the relevant site

DOP, Diabetes in low-resource Populations.

**Figure 1 F1:**
[figure not shown]
Participant’s flow. CGM, continuous glucose monitoring; DM, diabetes mellitus;
FPG, fasting plasma glucose; HbA1c, glycated haemoglobin; NGT, normal glucose
tolerance; OGTT, oral glucose tolerance test.

Study phases: this study will consist of overlapping phases, as described in table 2.

**Table 2 T2:** Implementation phases (I–IV)

Phase I	The first phase involves conducting the main baseline survey, whose outcomes are the prevalence of diabetes, pre-diabetes and associated risk factors, and glucose tolerance subgroups based on WHO criteria. This phase will include the following activities: Research team selection and training Stakeholder and community sensitisation Mobilisation and participant notification Recruitment of participants Obtaining consent and baseline questionnaire data collection Anthropometric measurements Baseline OGTT Blood and urine sample collection We will use systems already in place for the GPC cohort to achieve and maintain high levels of participation. These systems include: GPC census/survey teams, meeting the community advisory board, meeting local leaders, organising community meetings and participant notification.
Phase II	This phase involves the assessment of the reproducibility of the diagnostic approaches in a randomly selected set of participants. In this phase, we shall assess the diagnostic reproducibility of the fasting glucose and OGTT (diagnostic reproducibility substudy). We will determine whether participants with isolated impaired fasting glucose and isolated impaired glucose tolerance have elevated blood glucose in day-to-day living, compared with normoglycaemic individuals using continuous glucose monitoring. This phase will involve the following activities: Repeat OGTT Continuous glucose monitoring
Phase III	This phase aims to assess and describe any diabetes clusters or phenotypes by comparing baseline characteristics, and evaluating the distribution of various measures inclusive of biochemical parameters (eg, fasting and stimulated C peptide), adiposity and anthropometric indices. Further tests, including vascular complications assessment, endogenous insulin secretion measurement and islet autoantibodies profiles, will be done in future to better understand the differences between the various diabetes phenotypes.
Phase IV	In this phase, we aim to establish well-characterised people with and without diabetes. The newly diagnosed participants with diabetes will be referred to the local diabetes clinics, where they will be managed according to the Uganda Ministry of Health guidelines. The newly diagnosed patients with diabetes and those with known diabetes will be followed up in clinics (supported by the research team) to study the *course of the condition*, including; (1) response to treatment: participants will be followed up at the clinic to assess glycaemic control (HbA1c) every 3 months, determine the time to treatment intensification (need for dosage increment, the addition of another drug or switching from oral hypoglycaemic agents to insulin), and (2) assess disease progression *through* (a) measuring of endogenous insulin secretion (using mixed meal tolerance tests), (b) assessment of insulin resistance and repeat vascular complications reassessment (including retinopathy, nephropathy). Concurrently, participants with pre-diabetes and those with normal glucose levels will be followed in a longitudinal study nested in the GPC to determine the incidence of diabetes.

GPC, general population cohort; HbA1c, glycated haemoglobin; OGTT, oral glucose
tolerance test.

### Data collection

Data will be collected on social demographics (age, sex and marital status),
socioeconomic (household assets, household income, level of education and occupation),
lifestyle (diet, physical activity, smoking and alcohol consumption) and family history of
the disease (diabetes, hypertension, dyslipidaemia, coronary heart disease, stroke, renal
disease, diabetes-related eye disease, HIV status, tuberculosis, malaria and other chronic
infections such as hepatitis C virus). Data on biophysical measurements will be collected,
including: height, weight, total body fat, skeletal muscle mass, visceral fat, waist and
hip circumferences, mid-upper arm circumference (MUAC) and calf circumference, blood
pressure and pulse.

### Patient and public involvement

Patients, community representatives and policymakers are engaged at different stages of
our research including formulating research questions. We have community advisory groups
to facilitate our engagement with the community.

### Study procedures

#### Biophysical measurements

Standing height will be measured with a Seca stadiometer to the nearest 0.1 cm.
The sitting height will be determined by measuring the distance from the sitting surface
to the top of the head using a Seca stadiometer and a flat-seated seat, with the sitting
surface centred and placed against the backboard of the stadiometer. Weight will be
measured in light clothing with a Seca 761 mechanical flat scale (spring-type scale) to
the nearest 0.1 kg. The scale will be placed level on a hard surface.

Total body fat, skeletal muscle mass and visceral fat will be measured with an OMRON
KaradaScan, Body Composition Monitor Bio-impedance scale (OMRON Healthcare Company
Limited, Japan). Waist and hip circumferences will be measured with a Seca 201 measuring
tape to the nearest 0.1 cm. Waist circumference will be taken from the narrowest
part of the abdomen between the ribs and the iliac crest (top of the hip bone). Hip
circumference will be measured as the tape is placed around the most protruding part of
the buttocks. MUAC will be measured with a MUAC measuring tape to the nearest
0.1 cm at the midpoint level between the tip of the acromion and the
olecranon.

Calf circumference will be measured with a Seca 201 measuring tape to the nearest
0.1 cm. The circumference of the calf will be measured at its widest point
perpendicular to the long axis of the calf to the nearest 0.1 cm. Skinfold
thickness over the triceps muscle will be measured with a Harpenden skinfold calliper.
Skinfold thickness will be measured at the posterior surface of the upper arm over the
triceps muscle at the midpoint between the acromion and the olecranon process of the
right arm. Blood pressure and pulse will be measured three times with resting intervals
of 5 min using an automated upper arm blood pressure monitor (OMRON, Healthcare
Europe, the Netherlands).

#### Continuous glucose monitoring

Continuous glucose monitoring (CGM) will be carried out using the blinded Freestyle
Libre Pro Flash Glucose Monitoring System (Abbott Laboratories, Illinois, USA), a
professional CGM device which records interstitial glucose every 15 min for up to
2 weeks.

#### OGTT and biological sample collection

The OGTT will be performed following the WHO guidelines. The study nurse will confirm
if the participant fasted overnight for at least 8 hours. Baseline fasting blood
samples will be collected for fasting plasma glucose measurement and biobanking for
future diabetes and related studies. Following the collection of the fasting blood
samples, a standard 75 g of glucose will be administered, and a repeat blood
sample will be collected after 120 min. Participants who have not fasted
appropriately will be asked to return in a fasted state on another day.

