### Definitions

Diabetes will be defined according to WHO guidelines as a fasting venous capillary plasma
glucose ≥7.0 mmol/L, a 2-hour post-load venous plasma glucose
≥11.1 mmol/L, HbA1c ≥48 mmol/mol (6.5%) or on oral or
insulin treatment for diabetes. Pre-diabetes will be defined as a fasting venous or
capillary plasma glucose between 5.6 and 6.9 mmol/L, a 2-hour post-load venous
plasma glucose between 7.8 and 11.0 mmol/L or HbA1c between 42 and
47 mmol/mol (6.0–6.4%).^13–15^

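### The only OGTT preparation check written out is an 8-hour fast, which does not catch the missed or small evening meal that the protocol itself says could falsely raise glucose

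*Protocol article*

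**What the plan says.** **The hazard.** The Introduction notes that an OGTT depends on adequate food intake in the days before it. It then reports: "Our preliminary study showed that a missed or small meal the" "night before a test could lead to falsely elevated glucose". It suggests that this may explain high prevalence in some African studies that used OGTT, and concludes that OGTTs cannot be fully "relied on to screen for diabetes in settings where food insecurity or missed evening meals" are common.

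**The check.** Under *OGTT and biological sample collection*, the test is to follow WHO guidelines, and the study nurse confirms "if the participant fasted overnight for at least" 8 hours. Those who have not fasted "appropriately will be asked to return in a fasted state on another day". The section describes no question about the evening meal.

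**The use of the result.** *Definitions* begins "Diabetes will be defined according to WHO guidelines as a fasting venous capillary plasma" glucose of at least 7.0 mmol/L, and joins to this by *or* a 2-hour value of at least 11.1 mmol/L, an HbA1c criterion and current treatment. A 2-hour value of 7.8 to 11.0 mmol/L is likewise enough for pre-diabetes. The prevalence of both conditions is the primary outcome. The Introduction also says that with "this approach, we will be able to compare the diagnostic accuracy of fasting glucose and" HbA1c against OGTT.

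**The concern.** The written check guards against too short a fast. The hazard named in the Introduction is the opposite one: too little food the evening before. A person who missed that meal has fasted longer than required, so the check admits them and nothing written down marks them.

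Any resulting error runs upward. It can add cases to the primary prevalence, because the criteria are joined by *or* and no other criterion can remove a false 2-hour positive. It can also contaminate the comparator. People without diabetes who are falsely positive on OGTT and correctly negative on fasting glucose or HbA1c would count as misses by those tests. The sample-size section expects OGTT to add a large share of cases, so this route into the case count matters. A larger sample does not reduce a bias of this kind.

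**Working it through.** **1. The plan's own figure.** Inputs from *Sample size determination*: prevalence p = 0.05, margin d = 0.005, z = 1.96.

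n = z²p(1−p)/d² = 3.8416 × 0.0475 / 0.000025 ≈ 7299, which the plan rounds to 7300. Then (7300/0.8) × 1.2 = 10 950. Both figures reproduce. In reverse, 10 950 × 0.8 / 1.2 gives an effective sample of 7300. The sample size is not in error; the issue is bias.

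**2. Bias from the unmeasured meal.** Let m be the share tested after a missed or small meal, and f the share of the non-diabetic people among them who are falsely moved to 11.1 mmol/L or above. The documents give neither, so both are assumptions. Taking m to be the same in people with and without diabetes:

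bias = m × f × (1 − p)

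**3. When the bias equals the margin.** Setting bias = 0.005 with p = 0.05 gives m × f = 0.005 / 0.95 = 0.00526, or about 0.53% of non-diabetic participants.

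| Assumed m | f at which bias = 0.5 points |
|---|---|
| 5% | 10.5% |
| 10% | 5.3% |
| 20% | 2.6% |
| 30% | 1.8% |

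**4. Range.** Over m = 5–30% and f = 1–10%:

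- smallest: 0.05 × 0.01 × 0.95 = 0.0475 points in 100, or about 0.05 points;
- largest: 0.30 × 0.10 × 0.95 = 2.85 points.

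That is 0.1 to 5.7 times the planned margin.

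**5. Effect on the interval.** At an effective n of 7300, a nominal 95% interval would cover the true prevalence about 84% of the time with a bias of 0.25 points, and about 53% of the time with a bias of 0.5 points.

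**6. Effect on the accuracy comparison.** An index test that classified everyone correctly would show an apparent sensitivity of p/(p + bias) against the contaminated comparator. At a bias of 0.5 points this is 5/5.5 = 90.9%. Over the range in step 4 it runs from 99% down to 64%.

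**7. Pre-diabetes.** No figure is offered. A false rise moves some people into the 7.8–11.0 band and others out of it into diabetes. Some would already be counted through fasting glucose or HbA1c, and the documents do not give these overlaps.

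**The case against.** Several points stand against a stronger reading.

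- **The text says *could*.** A reader might infer that false positives do enter and that the prevalence will be inflated. The documents support only a possibility, reported from one preliminary study, with no frequency or size.
- **WHO guidelines are cited for the OGTT.** They may cover preparation, but their content is not in the article. So the 8-hour fast is the only check written out, not demonstrably the only one applied.
- **The article condenses a full protocol (version 1.2).** *Data collection* lists diet without its items. A reader might infer that nobody already tested has a meal record; the documents do not show that. The point survives condensation because the article states the hazard as its own result and then spells out a check and a rebooking rule that do not meet it.
- **The design has partial safeguards.** The Abstract provides repeat tests, before referral, for people identified with diabetes and for random controls. Phase II adds repeat OGTT, and continuous glucose monitoring that asks whether isolated impaired fasting glucose or isolated impaired glucose tolerance goes with raised glucose in daily life. The Abstract also lists OGTT among the tests whose utility is assessed, so it is not treated as beyond question. But these steps serve reproducibility and cover subsets. No rule reclassifies a case after them, and not all people with pre-diabetes are retested.
- **A distorted rural–periurban comparison** is also tempting to infer. It would need meal-skipping to differ between the sites, and the documents say nothing on that.

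**Conclusion.** The concern holds as a gap between the stated hazard and the stated check. As written, the plan has no described means of detecting or separating an upward bias that it names itself, and that bias can reach both the primary prevalence and the comparison of fasting glucose and HbA1c with OGTT.

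Its size is unknown. The benchmark of about 0.53% of non-diabetic participants rests on the plan's 5% prevalence taken as true and on the simple product of m and f; the 10% × 5.3% split is only an example. The textual gap is certain. That false positives occur, and in what number, is not established. The point merits a change to the plan but does not invalidate the design.

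**What to change.** 1. Reconcile the Introduction, *OGTT and biological sample collection* and *Definitions*, so that the stated limitation of OGTT and the way its result is used agree. If the WHO procedure or the full protocol already covers the evening meal, say so.
2. Have the nurse who confirms the fast also record the time and size of the last evening meal (none, small, usual).
3. Keep the all-participant prevalence as primary. Prespecify a sensitivity analysis by meal status of prevalence, and of the accuracy of fasting glucose and HbA1c against OGTT.
4. Report prevalence by criterion, so that cases resting on OGTT alone are visible. This uses measurements already planned.

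Whether to rebook people who missed the meal is for the study team.

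**Cost.** Two extra questions and one tabulation. Enrolment began in January 2022, so if meal status was not recorded earlier, the analysis by meal status covers later enrolment only. The subgroup with an adequate meal may under-represent food-insecure adults, so its estimate should sit beside the main one and not replace it.
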